#### Auditing

Because the intervention can be classified as “minimally invasive intervention,” no formal auditing will be conducted.

### Ethics and dissemination

#### Research ethics approval

The study protocol was approved by the ethics committee of Kyoto University Graduate School of Medicine (C1357) and will be approved by the ethics committees of other collaborating universities.

#### Protocol amendments

Any amendments to the protocol will be submitted to the ethics committee of Kyoto University Graduate School of Medicine for approval. Once approved, they will be reported to all the study investigators and, where necessary, to the study participants. Further approval of the ethics committees of participating universities will also be sought.

#### Consent or assent

We will employ a two-stage consent procedure. At the time of the annual health checkup, participants will have access to the recruitment web page explaining the smartphone app and the trial, fill in part I of the questionnaire, and provide their contact details to receive an invitation to the orientation meeting. At the orientation meeting, the researchers from the student health center will obtain the fully informed written consent to participate in the trial on the smartphone app. Because all participants will be at least 18 years of age and the intervention is minimally invasive, no assent or consent from authorized surrogates is assumed for this study.

#### Confidentiality

Each participant will receive an identification number, and all the records will be managed using these identification numbers. The security of the data transfer between the app and the server will be guaranteed by SSL, and the data will be stored on the secure server. The data management team will download the data regularly and store them using a medium that is not connected to the internet and is kept in a locked drawer. Once the trial is completed, the data on the server will be erased permanently. The consent forms and the medium storing the downloaded data will be kept in the locked drawer in the student health center for 10 years after the publication of the primary findings. The de-identified, anonymized dataset will be uploaded to the UMIN-ICDR website (http://www.umin.ac.jp/icdr/index-j.html), and researchers approved by the steering committee will be able to have access to the dataset.

#### Access to data

All members of the steering committee will have full access to the final trial dataset.

#### Ancillary and posttrial care

All the participants receive the standard care as provided by the student health center of Kyoto University and by corresponding facilities in each participating university, both throughout the study and afterward.

#### Dissemination policy

The full protocol will be published in an academic journal in English. Its Japanese synopsis will be posted on the website of the student health center and the Department of Health Promotion and Human Behavior, Kyoto University Graduate School of Medicine/School of Public Health.

The study results will be disseminated to health care professionals and the public through presentations in academic meetings and publications in academic journals. The synopses of these reports will be posted on the home page mentioned above for their dissemination to trial participants.

Authorship of the planned primary and secondary publications will include all the members of the steering committee and others judged as appropriate by the steering committee. The order of the authors will be determined by the steering committee in consideration of the contributions of each member. After the publication of the primary findings, the de-identified and completely anonymized individual participant-level dataset will be posted on the UMIN-ICDR website (http://www.umin.ac.jp/icdr/index-j.html) for access by qualified researchers.

## Discussion

We have described the protocol for a MOST fully factorial trial aimed at optimizing the smartphone CBT for university students. The primary objective of this study is to estimate the specific efficacy of each of the five cognitive or behavioral components to reduce psychological distress within 2 months and thereby to propose the most efficacious and efficient combination of components for university students. The study has several secondary objectives, including the exploration of matching between treatments and individual characteristics and the examination of the prophylactic effect of smartphone CBT to prevent an MDE over the course of 12 months.

There will be many challenges in the conduct of this large-scale trial, including the recruitment of participants and their retention in the smartphone CBT and in the assessment. We have taken measures to meet these challenges as follows. First, Kyoto University, the primary study site, has over 22,000 undergraduate and graduate students, and we are anticipating participation of several similarly sized universities. Second, we have incorporated several trial design features to increase retention [56]: a run-in period before randomization so that only those who have shown preliminary adherence to the program are randomized; measuring the primary outcome at a relatively early time point (2 months); measuring all the outcomes online with several prompts built into the smartphone app; and offering appropriate monetary incentives, as approved by the ethics committee, for the completeness of data collection. Finally, the research team has a good track record in enrolling and following participants in previous trials [18, 57–59].

The theoretical strength of the proposed trial is its ability to estimate the specific main effect of a cognitive or behavioral component by comparing combinations including that component against those not including that component, all of which are equivalent in terms of treatment credibility, delivered attention, or therapist allegiance that may contribute to nonspecific effects. These findings can be expected to uniquely contribute to the theories of psychotherapy and of CBT [60].

The pragmatic advantage of the proposed trial comes from the MOST framework, which involves optimization trials using highly efficient experimental designs. This framework enables the investigator to identify the most efficacious and efficient package for a complex intervention. The resultant package of smartphone CBT can be efficiently delivered to a large number of students and attain the largest efficacy benefit for them. We also expect to move on to the evaluation phase of the MOST design in the future, in which we can not only evaluate this optimized intervention against treatment as usual but also collect further information to personalize the treatment to match the individual student’s characteristics and needs.

We will start the recruitment in 2018 and aim at completing the trial by 2021, and we expect to start publishing the results soon afterward.

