In this study, we use the three cognitive behavioral components for SM, CR, and BA that were included in an internet CBT program with demonstrated effectiveness [18] and two similarly constructed components for AT and PS. This study represents the optimization phase according to MOST and uses the fully factorial design that allows estimation of main effects of individual components and their interaction effects. In this design, the effect of a component is estimated by comparing the mean of all combinations including that component against the mean of all other combinations not including that component. Because both the former and the latter sets of combinations have equal credibility and nonspecific supportive elements, this design allows estimation of effects specific to that component and can uniquely overcome the issue of specificity in psychotherapy research [22], which has been unable to find a nonspecific control equal to pill placebo in drug research [23, 24] and has had formidable difficulties in elucidating effects specific to a certain intervention over and above nonspecific psychotherapies. A further challenge associated with multicomponent interventions is matching particular components with individual characteristics: Some components may be particularly fit or unfit for certain subgroups of participants. There have been several attempts to tailor or personalize psychotherapies to match individual characteristics [25, 26]. Smartphone CBT offers a unique opportunity to examine effect modification by individual characteristics because it enables recruitment of the large sample of participants that would be required to examine the issue.

The purpose of the Healthy Campus Trial is therefore to examine specific efficacy of CBT components, thereby determining the most effective and efficient combination for university students and exploring the matching of the selected components with individual characteristics. Given the long-lasting and potentially serious consequences of psychological distress, the study will have two analytical phases: analysis 1 (stress reduction study) and analysis 2 (prevention study).

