## Methods/design

### Objectives

The primary objectives of analysis 1 are twofold:To find if each component has specific efficacy in terms of short-term (2 months) alleviation of psychological distress, including depression and anxiety. The biggest strength of the factorial design is that the examination of each component as a main effect can reveal the specific efficacy of that component in comparison with not receiving that component.To find the most efficacious components and the most efficient combinations thereof out of the five typical CBT skills for the university students. The identified combinations should be efficient in terms of the time and effort required of the students and the costs incurred by the university.

The trial is also designed to answer the following ancillary questions:3.To conduct exploratory analyses to find the best matches between students’ baseline characteristics and the CBT components so that we can offer personalized and improved services in the future.4.To examine the ordering effect of BA and CR, the two most basic components of CBT.5.To explore the process variables in the efficacy of the smartphone CBT.6.To test for enduring effects of the 2-month stress reduction at 12 months.

The target population of analysis 1 is those students with elevated distress at baseline, defined as scoring 5 or more on the Patient Health Questionnaire-9 (PHQ-9) [28].

The primary objectives of analysis 2 are as follows:To examine the long-term effect (12 months) of the most efficacious and efficient combination(s) in preventing future occurrences of new depressive episodes.To examine the ordering effect of BA and CR and to explore the process variables in the efficacy of the smartphone CBT in preventing future occurrences of new depressive episodes.

The target population of analysis 2 is those without a major depressive episode (MDE) as ascertained by Composite International Diagnostic Interview (CIDI) at baseline.

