### Anticipated risks and benefits for the participants

The interventions will consist of various amounts of PE and exercises in cognitive and behavioral skills for stress reduction to be conducted as self-help by the participants on their smartphones. The interventions will therefore be considered as “intervention with minimal invasiveness,” and no serious health risks are expected, except for possible psychological and time burden in going through the program and responding to the questionnaires. On the contrary, a meta-analysis of internet-based guided self-help programs show that participants have lower risk of deterioration in symptoms of depression during such interventions than control groups [29].

The possible psychological and time burdens will be fully disclosed and explained to the potential participants at the orientation meeting, and only those who have provided written informed consent will be recruited into the study. No insurance scheme is therefore planned.

However, possibility of serious adverse events (SAEs), whether related to the study participation or not, cannot be negated as would be normally would be expected of participants leading their university student lives. They will be closely monitored, and all participants will be provided standard care through the student health center at the university. Any expenses necessary for such services will be handled as usual. On the other hand, the participants can expect to learn about psychological stress and about how to maintain mental health through the program. But the extent of such benefits is the theme of this trial and is currently unknown.

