#### Blinding

Neither the participant nor the study personnel will be blinded to the intervention that each participant is receiving through the conduct of the trial. The assessment of all the primary and secondary outcomes is self-report by the participant and therefore not blinded. The statisticians will be blinded to the allocation through the statistical analyses by analyzing the datasets prepared by the study personnel in which all components are denoted only by a letter. The writing committee will review the statistical analysis report without knowledge of the identification of the components, which will be revealed only after the writing committee signs off the agreed-on statement of interpretation.

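### The Background and Discussion claim equal attention with and without a component, but Table 1 allocates one more lesson to the with-set, so a main effect alone cannot show a component-specific effect

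*Protocol article*

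**What the plan says.** The Background describes the main-effect contrast as "comparing the mean of all combinations including that component against the mean of all other combinations not including that component". It then states that "both the former and the latter sets of combinations have equal credibility and nonspecific supportive elements", and concludes from this that the design estimates effects specific to a component and overcomes the specificity problem in psychotherapy research. The Discussion repeats the argument as the trial's theoretical strength, describing the combinations compared as "all of which are equivalent in terms of treatment credibility, delivered attention, or therapist allegiance that may contribute to nonspecific effects". Under Objectives, the first primary aim of analysis 1 is the specific efficacy of each component, and the main effect is said to be one that "can reveal the specific efficacy of that component in comparison with not receiving that component".

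Other sections describe what is delivered:

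- **Interventions and Table 1.** Each component is one lesson, nominally one week. The next lesson opens only after a week has passed and one worksheet is done. Everyone receives PE before randomization. An absent component leaves a blank in the sequence, and C63 and C64 contain PE only.
- **Anticipated risks and benefits for the participants.** This section says that the amount varies: "The interventions will consist of various amounts of PE and exercises in cognitive and behavioral skills for stress reduction".
- **Blinding.** "Neither the participant nor the study personnel will be blinded to the intervention that each participant is receiving", and all primary and secondary outcomes are self-reported.
- **Strategies to improve adherence.** A weekly semiautomated email congratulates participants on their progress.

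**The concern.** The inference to a specific effect needs the two sides of each contrast to carry the same nonspecific ingredients. If an absent component is simply left out, the side with the component gets one more lesson, one more worksheet and more time in the program. Any benefit of having one more lesson, whatever its content, then enters that component's main effect, and it does so for all five components alike.

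At stake is what a significant main effect can be said to show. It shows that adding the component helped. Without equal attention, it does not show that the component's content helped beyond the extra engagement, which is the theoretical claim made in the Background and Discussion.

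**Working it through.** **1. The plan's own figure.** Sample size states 1051 for a standardized difference of 0.20, two-sided alpha 0.05 and power 0.90. Total N = 4 × ((1.960 + 1.282)/0.20)² = 1050.7, so the figure reproduces. Rounding up to 17 per combination gives 17 × 64 = 1088. The point below does not affect these numbers.

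**2. Lessons per combination.** Counting post-PE lessons in the 64 sequences of Table 1 (the sequences agree with the +1/−1 columns throughout):

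| Lessons after PE | 0 | 1 | 2 | 3 | 4 | 5 |
|---|---|---|---|---|---|---|
| All 64 combinations | 2 | 10 | 20 | 20 | 10 | 2 |
| 32 with a given component | 0 | 2 | 8 | 12 | 8 | 2 |
| 32 without it | 2 | 8 | 12 | 8 | 2 | 0 |

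The last two rows are the same for SM, CR, BA, AT and PS.

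- Mean with: (2×1 + 8×2 + 12×3 + 8×4 + 2×5)/32 = 96/32 = 3.0.
- Mean without: (2×0 + 8×1 + 12×2 + 8×3 + 2×4)/32 = 64/32 = 2.0.
- Counting PE, the means are 4.0 and 3.0, the same gap of one lesson.
- At the minimum of one week per lesson, this is 3 versus 2 weeks. At the 10.8 days per lesson that the protocol cites from its earlier trial, it is 3 × 10.8 = 32.4 versus 2 × 10.8 = 21.6 days.

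C63 and C64 lie in the without-set of all five components; C1 and C2, with five lessons, lie in the with-set of all five.

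**3. Can adjustment separate content from lesson count?** No. The allocated lesson count equals 2.5 + 0.5 × (sum of the five codes) exactly, with zero residual. It is a linear function of the five factors already in the model.

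**4. Illustration of size (the per-lesson effect is an assumption; no document gives one).** With unit residual SD, the SE of a main effect is 2/√1088 = 0.061. Suppose each lesson carried only a nonspecific effect of g SD, additive across lessons. Every main effect would then equal g, and the chance that a given component reaches p < 0.05 would be:

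| g (SD, assumed) | 0.05 | 0.10 | 0.15 |
|---|---|---|---|
| Probability | 13% | 38% | 70% |

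**5. A contrast with equal lesson counts.** The difference between the main effects of A and B reduces to the mean of combinations with A but not B, minus the mean of those with B but not A. Each side has 16 combinations, 16 × 17 = 272 participants, and an average of 1 + 3 × 0.5 = 2.5 lessons. Its SE is √(2/272) = 0.086 SD, which gives 90% power at (1.960 + 1.282) × 0.086 = 0.28 SD.

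**The case against.** The strongest reply has four parts.

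- **Attention may mean scheduled contact.** Weekly emails, weekly PHQ-9 to week 8, reminders and payments are described without reference to lesson count. The text does not say whether emails continue after a short allocation is finished, so the emails are not evidence of unequal contact. This stands, but it does not rescue the sentence. The protocol does not define attention so narrowly, and the Background claims equality of nonspecific supportive elements in general. An extra lesson with a worksheet is itself engagement.
- **Table 1 says nothing about credibility or allegiance.** This stands. A reader might infer that Table 1 refutes the whole sentence. It refutes the part on attention and time. Equal credibility is unsupported, and open to doubt when some students get no lesson after randomization, but it is not disproved. Therapist allegiance is not affected.
- **The gap is allocated, not received.** The protocol expects fewer participants to complete later parts, so the received difference may well be under one lesson. This stands; the figures here are allocated lessons.
- **The estimand is already clear and serves the purpose.** Objectives compares receiving with not receiving the component, and choosing components is the stated emphasis of the optimization phase. This also stands. A reader might infer that the selection of components is invalid. The documents do not support that: the total effect of adding a lesson is relevant to deciding whether to include it.

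**Conclusion.** The Background and Discussion state a property that the design does not have. The combinations with and without a component differ by exactly one allocated lesson on average (3.0 versus 2.0 after PE), for all five components. The statement on amounts under Anticipated risks and benefits agrees with Table 1, not with the claim of equality. The main effect is a valid estimate of adding the component versus not receiving it, and remains usable for selection. Alone, it cannot support efficacy over and above the nonspecific effect of one more allocated lesson.

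The lesson counts are exact and need no assumption. How far a nonspecific effect would move the results is not known. The 13%, 38% and 70% figures rest on assumed per-lesson effects of 0.05, 0.10 and 0.15 SD, additive accumulation, full uptake and a component with no specific effect. A reader might take them as this trial's false-positive rate; they are illustrations only. The sample size and the planned model are unaffected.

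**What to change.** In the Background and Discussion, delete the statement that the sets are equal in delivered attention and nonspecific elements, and present equal credibility only as an assumption. There, and where Objectives and the Discussion speak of specific efficacy, describe the main effect as the effect of adding the component, including its extra lesson of time and engagement. This costs a few sentences and changes no data, model or sample size.

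Optionally, report pairwise differences between component main effects from the planned model as a supportive analysis. They need no new data and compare sets with equal lesson counts. They have limits:

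- They are less precise than a main effect (SE about 0.086 against 0.061 SD).
- They are relative, so five equally specific components would show no difference.
- They cancel the nuisance only if its effect is the same whichever lesson is given.

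For these reasons they should not be a required test of specificity.

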### Trial status

Participant recruitment was started in April 2018 and is ongoing at the time of submission of this protocol paper.

## Abbreviations

ANCOVA: Analysis of covariance
AT: Assertion training
BA: Behavioral activation
CBT: Cognitive behavioral therapy
CIDI: Composite International Diagnostic Interview
CR: Cognitive restructuring
DSM: *Diagnostic and Statistical Manual of Mental Disorders*
DSMB: Data and Safety Monitoring Board
GAD-7: Generalized Anxiety Disorder-7
HPQ: Heath and Work Performance Questionnaire
MDE: Major depressive episode
MOST: Multiphase optimization strategy
PE: Psychoeducation
PHQ-9: Patient Health Questionnaire-9
PS: Problem solving
RCT: Randomized controlled trial
SM: Self-monitoring
SSL: Secure Socket Layer
WHO: World Health Organization
